	# promoted foods purchased/consumed by BHCK participants
	# of giveaways received by BHCK participants
	# units of promoted foods sold
Adult/household (SMS)	Household food purchasing (healthy and unhealthy foods)
	Healthiness of common methods of food preparation
	Change in psychosocial factors (knowledge, self-efficacy, intentions)
	Change in weight, BMI
Children and Youth Leaders	Frequency of purchase of healthy and unhealthy foods
	Healthiness of food preparation methods
	Change in dietary patterns (e.g., total calories, total fat, FV servings, HEI scores, etc.)
	Change in psychosocial factors (knowledge, self-efficacy, intentions, outcome expectations)
	Change in BMI percentile

A sample of adult caregiver-child dyads (n = 24 dyads per zone, 720 at baseline) will be surveyed pre- and post-intervention to assess impact. The first section of the adult instrument contains questions pertaining to household size and composition, and use of community recreation centers by children. Specific food sources visited for purchasing/getting foods and amount of money spent at each source is recalled for the last 30 days. Frequency of purchase of 40+ non-prepared foods in the last 30 days is recalled (fruits, vegetables, chips, soda, chicken, etc.). The next section asks how many times a meal was prepared for the household in the last 30 days, and inquires about the top three most common preparation methods of seven types of foods (chicken, fish, potatoes, etc.). A series of self-efficacy questions assess confidence in performing healthier behaviors along a 4 point ordinal scale. Eight questions about behavioral intentions about food are asked (i.e., “The next time you fried an egg, what would you use to fry it? a) Cooking Spray; b) Oil; c) Butter, Margarine, Shortening, or Lard.” Ten food-related knowledge questions are asked. The next section asks a series of questions about health beliefs and attitudes using a Likert scale, i.e. “Health foods are tasteless. Do you Strongly Disagree, Disagree, Undecided, Agree, or Strongly Agree?” Adult respondents are questioned about their food assistance participation and are asked to provide basic socioeconomic information (education level, income category). The last section of the survey contains the 18 question USDA food security questionnaire [45].

The child interview consists of two instruments – the Block Kids 2004 Food Frequency Questionnaire (FFQ) and a Child Impact Questionnaire (CIQ). The Block Kids 2004 FFQ instrument is a validated FFQ (Nutrition Quest, Berkeley, CA) that asks about frequency and portion of consumption of 77 food items as is based on NHANES 1998–2002 data [46]. The CIQ consists of 79 questions pertaining to demographics, food purchasing, food preparation, intentions about food, outcome expectancies, self-efficacy, food knowledge, social support, and breakfast consumption. Demographics including age, birthdate, sex, race, and contact information are obtained. Specific food sources visited, number of times patronized, and who the child most frequently shopped within the last seven days is recalled. Frequency and location of purchase of 65+ non- prepared and prepared food items is recalled for the last seven days (beverages, fruits and vegetables, groceries, fast food, snacks, etc.). The next section of the questionnaire assesses how often a member of the household prepared food for the child and how often the child prepared food for themselves in the last seven days. If a child prepared food for themselves, information on types of food prepared and methods of preparation utilized are collected. Twelve questions about behavioral intentions about food are asked (i.e. “If you wanted a snack, which would you choose? a) Potato chips; b) Pretzels; c) Yogurt). Eleven questions on both short-term and long-term outcome expectancies related to consumption of healthy and unhealthy foods are asked (i.e. I would be healthier if I ate French fries three times a week instead of eating French fries seven days a week. Is this a) True; b) Mostly true; c) Mostly false; or d) False). A series of twelve self-efficacy questions assess confidence in performing healthier behaviors along a 4 point ordinal scale. Fourteen food-related knowledge questions are asked. The survey contains two social support scales. The first scale consists of seven questions that inquire whether the child has someone in their life that would support healthier food and physical activity habits, who that person is, and whether they are older, younger, or around the same age as the child. The second social support scale consists of fourteen questions and asks how often the child’s parents and peers exhibit certain behaviors that support healthy and unhealthy eating using a Likert scale. The final section assesses frequency of breakfast consumption and includes a 24-hour recall of breakfast consumed the previous day. Anthropometric data (height and weight) are collected from both the caregiver and the child using a Seca 213 Portable Measuring Rod stadiometer and a Tantia BF697W Duo Scale.

At the store-level, sales data will be collected in two ways. Before, during and after the intervention, a BHCK staff member will ask store owners approximately monthly to recall sales of selected food items (promoted and non-promoted foods) in the last 7 days. Additionally, some of the wholesalers with which we partner will provide the BHCK team with specific sales data from accounts (stores) throughout the intervention. Wholesalers have agreed to provide sales data on promoted foods for BHCK participating corner stores and carryouts.

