**Methods:**

The B’More Healthy Communities for Kids (BHCK) intervention is a multi-level, multi-component intervention, targeting low-income African American youth ages 10–14 and their families in Baltimore, Maryland. This intervention prevents childhood obesity by working at multiple levels of the food and social environments to increase access to, demand for, and consumption of healthier foods. BHCK works to create systems-level change by partnering with city policy-makers, multiple levels of the food environment (wholesalers, corner stores, carryout restaurants), and the social environment (peers and families). In addition, extensive evaluation will be conducted at each level of the intervention to assess intervention effectiveness via both process and impact measures.

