**B’More healthy communities for kids conceptual framework.**

## Methods/design

The BHCK trial uses a group randomized study design, where 30 low-income, geographic zones surrounding recreation centers have been selected to serve as either intervention or comparison areas. All areas were required to be predominantly low-income and African American. Half of these zones have been randomized to intervention (Healthy Eating Zones (HEZs)), while the other half have been set to comparison (delayed intervention), in two waves. The center point (recreation center) of all intervention and comparison zones must exceed one mile in distance from each other, to reduce the potential for contamination.

The research was approved by the Johns Hopkins Bloomberg School of Public Health Institutional Review Board. Written informed consent was obtained from all adult participants for themselves, and for children. Written assent was obtained from all children who were part of the evaluation sample.

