### Sample size and statistical methods

We used baseline data from our previous trial, Baltimore Healthy Stores, regarding adult food purchasing to calculate sample size and study power to address the second hypothesis. Based upon our sample size calculations, we will need to have a sample size of 720 adult caretaker-child dyads (this is equivalent to 24 dyads from each HEZ) for the intervention assessments. Assuming a 15-20% drop-out after two years, this will leave us with a minimum of 600 adult caretaker-child dyad respondents post-intervention. We will be able to detect a 4–6 point change in our frequency of healthy food purchasing score, reflecting one healthy food purchased once a week.

For children participants in the dyads, sample size and power for program impact on children’s diet was calculated using national data on low-income urban AA youth diet. Within each selected household, we will randomly sample one child in the 10–14 year age range. Assuming 600 child respondents post-intervention, we will be able to detect a 320–450 difference in caloric intake, a difference of 12–15 g of fat intake and a difference of 1–1.5 percentage points in percent of energy from fat.

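### Change in BMI percentile is the only child weight outcome, and that scale gives little weight to change in obese children; a baseline-adjusted BMI z-score plus a scale without a ceiling would serve better

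*Protocol article*

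**What the plan says.** The Abstract of the protocol article gives the purpose: "This intervention prevents childhood obesity by working at multiple levels of the food and social environments". Table 2 sets out the impact outcomes by intervention level. In the row for children and youth leaders the weight-status entry is "Change in BMI percentile". It is the last of five entries; the other four cover food buying, food preparation, diet and psychosocial factors. For adults the same table has "Change in weight, BMI", which are scales without an upper bound. The article mentions no raw BMI, BMI z-score or distance from a cut-off for children, and it ranks no outcome as primary.

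The raw data for other scales are already planned. In the Measurements section, "Anthropometric data (height and weight) are collected from both the caregiver and the child", and for the child interview "Demographics including age, birthdate, sex, race, and contact information are obtained".

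The section on sample size and statistical methods bases its calculations on adult food purchasing and on children's diet. It gives no standard deviation, effect size or power for any child BMI measure.

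**The concern.** A BMI percentile is the normal distribution function applied to a BMI z-score. It is close to linear in the middle and nearly flat at the top. When changes in percentile are averaged over children, each child's change is in effect weighted by the slope of that curve at the child's starting point. A child near the median counts a great deal. An obese child with the same change in relative BMI counts for little.

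That fits poorly with a trial aimed at obesity. A benefit confined to the heaviest children would barely move the mean, and a mean that did move would mostly describe children in the middle of the range. The article names the scale itself, so this is a stated choice and not a detail left to another document.

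**Working it through.** The article gives no figure for BMI percentile, so there is nothing of its own to reproduce. The check is on the scale.

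**1. Equal change in relative BMI.** Percentile = 100 × Φ(z). A fall of 0.2 SD from z is worth 100 × [Φ(z) − Φ(z − 0.2)] points. The 0.2 is illustrative.

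| Start | From | To | Points lost | Weight relative to the median |
|---|---|---|---|---|
| z = 0 | 50.00 | 42.07 | 7.93 | 1 |
| z = 1.036 (85th) | 84.99 | 79.84 | 5.15 | 1/1.5 |
| z = 1.645 (95th) | 95.00 | 92.58 | 2.42 | 1/3.3 |
| z = 2 | 97.72 | 96.41 | 1.32 | 1/6.0 |
| z = 2.5 | 99.38 | 98.93 | 0.45 | 1/18 |
| z = 3 | 99.87 | 99.74 | 0.12 | 1/66 |

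The slope, 100 × φ(z), tells the same story: 39.9 points per SD at the median, 10.3 at the 95th percentile, 5.4 at z = 2 and 1.75 at z = 2.5.

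**2. Equal change in BMI units.** Step 1 defines equal change on the z scale, which flatters the z-score by construction. So the comparison was repeated in BMI units with the LMS (Box-Cox) form, z = [(BMI/M)^L − 1]/(L × S). The article names no growth reference, so the parameters are assumptions: M = 18, L from −1.5 to −2.5, S from 0.12 to 0.16. For L = −2 and S = 0.14, a fall of 2 BMI units is worth:

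| Starting BMI | z-score | Percentile points |
|---|---|---|
| 20 | 0.679 | 25.13 |
| 25 | 0.336 | 4.05 |
| 30 | 0.190 | 0.69 |
| 35 | 0.118 | 0.17 |
| 40 | 0.078 | 0.06 |

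From BMI 20 to BMI 40 the z-score shrinks the change by 0.679/0.078 ≈ 9 times, and the percentile by 25.13/0.06 ≈ 400 times. Over the assumed range the z-score ratio runs from about 6 (0.812/0.134) to about 13 (0.579/0.046). The percentile ratio is never below about 115 (21.87/0.19).

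With negative L the z-score also has an upper limit, −1/(L × S). This is 1/(2 × 0.14) = 3.57 here, and 2.50 to 5.56 over the range. The z-score is much less compressed than the percentile, but still compressed.

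**3. What this could do to a mean.** No child BMI distribution is given, so this step is illustration only. Suppose baseline z is normal with SD 1.1 and mean between 0.5 and 1.0, and every child falls by 0.2 SD. Children above the 95th percentile are then 15% to 28% of the sample but supply 3% to 6% of the mean percentile change. If only they improved, the sample mean would move by 0.17 to 0.28 points. With mean 0 and SD 1, they are 5% of the sample and supply 1.2% of the change (0.07 points). The size depends on the assumed distribution; in each case their contribution is about a fifth to a quarter of their share.

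**The case against.** The strongest reply is that this is one entry among several unranked outcomes in a condensed article, and that the trial is about prevention. No BMI criterion for enrolment is stated, and normal-weight and overweight children are also its target. The Background cites an earlier school-and-community programme whose result was reported as BMI percentile, so the scale allows comparison. At the 85th percentile the loss of weight is only 1.5-fold; the large ratios start well above the 95th. All of this stands. It limits the point to the choice of scale, and it is a reason to keep percentile for description. It does not make percentile a good scale for analysing change in a trial concerned with obesity.

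A reader might infer four stronger things that the document does not support.

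- That many of the enrolled children sit where the scale is flat. The prevalence figures in the Background are for adults, and none is given for the children.
- That the trial as a whole will be judged on this measure. It is the sole child weight outcome, but it is not called primary.
- That a z-score hides nothing. Step 2 shows that it still compresses change at very high BMI.
- That the sample-size section is at fault for giving no detectable difference in child BMI. It already says that the calculations rest on purchasing and diet. A figure for BMI z-score would need a standard deviation and an intracluster correlation that the article does not give.

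**Conclusion.** The point holds as a criticism of the stated scale. A change of 0.2 SD counts about 3.3 times less at the 95th percentile than at the median, 6 times less at z = 2 and 18 times less at z = 2.5. These ratios rest only on the normal form of the percentile and the illustrative 0.2.

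The effect on the trial's mean difference or power cannot be computed from the document, because it depends on the children's BMI distribution. It would therefore go too far to say that the trial will miss a benefit. The advantage of a z-score over a percentile is large but partial, and its exact size depends on the growth reference, which is assumed here. This is a worthwhile improvement to one outcome, not a contradiction or a miscalculation in the article.

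**What to change.** Define the child adiposity outcome as age- and sex-specific BMI z-score at follow-up, adjusted for baseline z-score, and name the growth reference. Add one scale without a ceiling, either BMI as a percent of the 95th percentile or BMI adjusted for age and sex, so that change at very high BMI is visible. Keep BMI percentile for description and for comparison with earlier trials.

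The cost is one or two extra derived variables and a change of wording. Height, weight, birthdate and sex are already collected, so no new measurement is needed. The main result will compare less directly with earlier work reported in percentiles, which keeping the descriptive percentile largely offsets.

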### Sample size and statistical methods

We used baseline data from our previous trial, Baltimore Healthy Stores, regarding adult food purchasing to calculate sample size and study power to address the second hypothesis. Based upon our sample size calculations, we will need to have a sample size of 720 adult caretaker-child dyads (this is equivalent to 24 dyads from each HEZ) for the intervention assessments. Assuming a 15-20% drop-out after two years, this will leave us with a minimum of 600 adult caretaker-child dyad respondents post-intervention. We will be able to detect a 4–6 point change in our frequency of healthy food purchasing score, reflecting one healthy food purchased once a week.

For children participants in the dyads, sample size and power for program impact on children’s diet was calculated using national data on low-income urban AA youth diet. Within each selected household, we will randomly sample one child in the 10–14 year age range. Assuming 600 child respondents post-intervention, we will be able to detect a 320–450 difference in caloric intake, a difference of 12–15 g of fat intake and a difference of 1–1.5 percentage points in percent of energy from fat.

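### The stated floor of 600 dyads after follow-up does not follow from 15–20% drop-out of 720, which leaves 576 to 612; the effect on the child detectable differences is about 1–2%

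*Protocol article*

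**What the plan says.** The Methods/design section of the protocol article describes a group-randomised design in which "30 low-income, geographic zones surrounding recreation centers have been selected to serve as either intervention or comparison areas", with half of the zones in each group. The Measurements section, in the text after Table 2, gives the survey sample as "n = 24 dyads per zone, 720 at baseline". The section on sample size and statistical methods repeats the total: "we will need to have a sample size of 720 adult caretaker-child dyads".

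That section then turns to attrition: "Assuming a 15-20% drop-out after two years, this will leave us with a minimum of 600 adult caretaker-child dyad respondents post-intervention". The next sentence gives the adult result, a detectable change of 4–6 points in the healthy food purchasing score, without saying which sample size it uses.

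The following paragraph covers the children and does name its sample size: "Assuming 600 child respondents post-intervention, we will be able to detect" a difference of 320–450 in caloric intake, 12–15 g of fat, and 1–1.5 percentage points of energy from fat.

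**The concern.** The drop-out range and the floor stand in the same sentence, and they disagree. A minimum has to hold at the worst end of the assumed range. Here the worst end is 20%, and the figure of 600 is not reached there.

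A retention floor tells the study team how much loss over two years the power statement can bear. As written, a 20% loss looks acceptable. At that loss, though, the trial would have fewer children than the number on which the child detectable differences are conditioned, and the differences it could detect would be somewhat larger than printed.

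**Working it through.** **Inputs, all from the protocol article**
- Zones: 30 (Methods/design).
- Dyads per zone: 24, total 720 (Measurements; Sample size and statistical methods).
- Drop-out: 15–20% after two years (Sample size and statistical methods).
- Stated floor: 600 (same section).
- Sample size for the child differences: 600 (same section).

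**Step 1. Baseline.** 30 × 24 = 720. The stated baseline total is reproduced.

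**Step 2. Retained sample.** Retained N = 720 × (1 − d).

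| Drop-out d | Retained dyads |
|---|---|
| 15% | 720 × 0.85 = 612 |
| 17.5% (midpoint) | 720 × 0.825 = 594 |
| 20% | 720 × 0.80 = 576 |

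The stated floor of 600 is not reproduced. The minimum over the range is 576, which is 24 dyads (24/600 = 4%) below it.

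**Step 3. Drop-out that gives 600.** 1 − 600/720 = 16.7%. This lies inside the assumed range, not at its upper end.

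**Step 4. Effect on detectable differences.** Hold the standard deviation, significance level, power and number of zones fixed, and assume even losses across zones. The detectable difference is then proportional to the square root of [1 + (m − 1) × ICC]/N, where m = N/30 is the number of dyads per zone. At N = 600, m = 20; at N = 576, m = 19.2. The article gives no ICC, so the non-zero values below are assumptions.

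- ICC 0: √(600/576) = 1.021.
- ICC 0.01: √[(1.182/576) / (1.190/600)] = 1.017.
- ICC 0.05: √[(1.91/576) / (1.95/600)] = 1.010.

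**Step 5. Applied to the printed child figures**

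| Measure | Printed, at 600 | At 576, ICC 0 | At 576, ICC 0.01 | At 576, ICC 0.05 |
|---|---|---|---|---|
| Caloric intake | 320–450 | 327–459 | 325–458 | 323–455 |
| Fat (g) | 12–15 | 12.2–15.3 | 12.2–15.3 | 12.1–15.2 |
| Energy from fat (percentage points) | 1–1.5 | 1.02–1.53 | 1.02–1.53 | 1.01–1.52 |

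If the adult change was also computed at 600, 4–6 points becomes about 4.1–6.1 without clustering. The article does not say that it was.

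The detectable differences themselves cannot be reproduced, because the article does not give the standard deviations, significance level, power or ICC. Only the ratio between the two sample sizes can be computed. A condensed article may leave those inputs to the full protocol, and their absence is not part of this point.

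**The case against.** The strongest reply is that the error hardly matters. The shortfall is 4% of the sample, and the detectable differences move by about 2% at most. The printed differences are themselves broad ranges. At the precision printed, the fat, percent-energy and adult purchasing figures round back to what the article already says, and the upper caloric bound moves by about 9. This stands, and it limits the point to a minor correction.

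A second reply is that the child statement is not false in itself. It is conditional on 600 respondents, and 600 is reached at a drop-out inside the assumed range. This also stands: the false statement is that 600 is a minimum. What remains is that the child figures apply only up to 16.7% drop-out, while the plan allows for 20%.

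A third possible reply is the replacement rule under Participants and recruitment, which draws the next eligible dyad when a selected one cannot complete the interview. That rule concerns selection from the recruitment list and does not clearly cover loss at follow-up, so it does not rescue the floor. Nothing else in the article reconciles the figures.

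Three stronger readings are tempting, and the document supports none of them:
- A reader might infer that the trial is seriously underpowered. A change of 1–2% in the detectable difference does not show that.
- A reader might infer that the baseline was inflated by multiplying by 1 + d where dividing by 1 − d was needed, since 600 × 1.20 = 720. The match is exact, but the article does not say how 720 was derived.
- A reader might infer that the adult 4–6 point change is also misstated. It follows directly after the 600 figure, but its sample size is not given, so this is a matter to check.

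**Conclusion.** The statement is wrong as written, and the consequence is minor. With 720 dyads and 15–20% drop-out, between 576 and 612 remain. The stated minimum of 600 holds only if drop-out is at most 16.7%. This part follows from the article's own figures and needs no outside assumption.

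At 20% drop-out the child detectable differences are optimistic by about 2.1% without clustering, and by about 1.0–1.7% at an assumed ICC of 0.05–0.01. Those percentages rest on even losses across zones and on otherwise unchanged design inputs. For the adult purchasing score the same effect is possible but not established.

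**What to change.** In the sample-size section, either:
- replace the floor of 600 with a retained sample of between 576 and 612, and restate the child detectable differences at 576; or
- keep 600 and state 16.7% as the maximum drop-out that delivers it.

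In either case, check which sample size the adult 4–6 point change used. If it was 600 and the first option is taken, restate it at 576 as well.

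The cost is a change of wording and, under the first option, one recalculation by the authors, who hold the inputs that the article does not print. The stated differences become slightly less favourable. Neither option needs extra participants. Guaranteeing 600 at 20% drop-out would instead need 600/0.80 = 750 dyads at baseline (25 per zone), but an effect this small does not call for it.
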